### 1.6.2. Part B (MAD), Cohorts 6-10

In Part B, up to 5 dose-escalation cohorts may be performed as outlined below. For Cohorts 7-10, dosing may be initiated after evaluation of cumulative safety, tolerability, and any relevant and available PK and/or PD data from all subjects enrolled in the previous cohort in Part B through Day 14.

| Cohort | Day -1          | Days 1-14                                                             |
|--------|-----------------|-----------------------------------------------------------------------|
| 6      | PTM capsule SD  | 0.5 mg TLC-2716 (1 x 0.5 mg) or PTM capsule, fed                      |
| 7      | PTM capsule SD  | 2 mg TLC-2716 a (1 x 2 mg) or PTM capsule, fed             |
| 8      | PTM capsules SD | 6 mg TLC-2716 a (3 x 2 mg) or PTM capsules, fed            |
| 9      | PTM capsules SD | 12 mg TLC-2716 a (2 x 5 mg; 1 x 2 mg) or PTM capsules, fed |
| 10     | PTM capsules SD | 20 mg TLC-2716 a (4 x 5 mg) or PTM capsules, fed           |

PTM = placebo-to-match; SD = single dose.

a The planned doses may be modified based on the observed safety, tolerability, and any relevant and available PK and/or PD data. Any modified dose will be within 3-fold of a dose previously tested.

### 1.6.3. Part C (Adaptive SAD and/or MAD), Cohorts 11-15

In Part C, the following optional cohorts may be performed:

| Cohort | Day -1*                     | Single Dose (Day 1) or Multiple Doses (Days 1-14)                                   |
|--------|-----------------------------|-------------------------------------------------------------------------------------|
| 11-15  | PTM capsule(s) QD or
BID | ≤ 50 mg total daily dose TLC-2716 or PTM, administered QD or
BID, fasting or fed |

BID = twice daily; PTM = placebo-to-match; QD = once daily.

\* Dosing of PTM on Day -1 will only be performed in multiple-dose adaptive cohorts (as in Part B).

## **2. ANALYSIS POPULATIONS**

The analysis populations in this study are defined as follows.

### **2.1. All Randomized Analysis Set**

All subjects randomly assigned to study intervention.

### **2.2. Safety Analysis Set**

All subjects randomly assigned to study intervention and who took at least 1 dose of study intervention. Subjects will be analyzed according to the initial intervention they actually received.

### **2.3. Pharmacokinetic Analysis Set**

All subjects randomly assigned to study intervention who took at least 1 dose of study drug and have sufficient plasma concentration data to reliably calculate PK parameters.

### **3. STATISTICAL CONSIDERATIONS FOR DATA ANALYSES AND HANDLINGS**

#### **3.1. Statistical Reporting**

In principle, analyses for safety will be summarized by the actual treatment group and analyses will be performed by subjects dosed with placebo and subjects dosed with TLC-2716 by cohorts for Part A and Part B. Subjects dosed with placebo will be analyzed as 1 group in each part. To assess the effect of food, analyses may be performed by fasting state and after a meal, as applicable.

Unless otherwise stated, continuous variables will be summarized by the number of non-missing observations, arithmetic mean, standard deviation (SD), median, Q1, Q3, minimum, and maximum values as summary statistics; categorical variables will be summarized by the frequency count and the percentage of subjects in each category.

All analyses will be performed using SAS Version 9.4 (SAS Institute, Cary, NC, USA).

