**Statistical Methods:**

**Safety:**

Safety data will be listed by subject and treatment and summarized by treatment for each cohort. As appropriate, data from placebo-treated subjects will be pooled across Parts A, B, and/or C.

Treatment-emergent AEs will be summarized by system organ class (SOC) and preferred term (PT) using the most current version of the Medical Dictionary for Regulatory Activities (MedDRA®). All AEs and all treatment-related AEs will be listed by treatment and subject. The frequency of subjects who experience AEs will be summarized overall within the cohort and by treatment. All AEs will also be summarized by relationship to study drug and severity.

Listings of individual subject laboratory results will be provided. Selected laboratory data will be summarized by cohort at scheduled visits and for the corresponding change from Baseline (Day 1 pre-dose for SAD cohorts in Parts A and C; Day -1 for MAD cohorts in Parts B and C). The incidence of treatment-emergent, graded laboratory abnormalities will be summarized by cohort and treatment.

Individual data for physical examination findings, ECGs, and vital sign measurements will be listed by treatment and subject, and summarized overall within the cohort and by visit, as applicable.

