### 3.1.3. Part C: Adaptive SAD and/or MAD (Cohorts 11-15)

Part C includes optional, adaptive cohorts to evaluate the safety, tolerability, PK, and PD of single- and/or multiple-ascending doses of oral TLC-2716 or placebo under fasted or fed conditions. Based on available safety, PK, and/or PD data generated in Part A and Part B, as applicable, doses for Part C (Cohorts 11-15) will be chosen, up to a total daily dose of 50 mg. Planned study treatments within each cohort are provided in [Table 4](#).

Part C will proceed in up to 5 dose-escalation cohorts and will be governed by a review of safety, tolerability, and any available and relevant PK and/or PD data generated from previous Part A, B, and/or C cohorts, as applicable.

- Randomized, blinded (sponsor-unblinded), placebo-controlled, single- and/or multiple-ascending doses of TLC-2716 with adaptive dose selection in healthy subjects. An attempt will be made to enroll at least 3 subjects in each cohort with Screening TG  $\geq$  150 mg/dL and/or low-density lipoprotein cholesterol (LDL-C)  $\geq$  130 mg/dL.
- Within each cohort, 10 unique subjects will be randomized 4:1 to receive up to a total daily dose of 50 mg TLC-2716 (N = 8) or PTM (N = 2) for either 1 day (as in Part A) or 14 days (as in Part B).

The frequency of dosing (QD or BID in MAD cohorts) and fasting versus fed status (in SAD or MAD cohorts) may also be modified versus Parts A and B. If dosing is administered in the fed state, standard meal conditions may also be modified at sponsor discretion. QD doses will be administered in the morning following a standard meal, and BID doses will be administered after a standard morning meal and evening snack, with the second dose administered 12 hours

(± 10 minutes) after the morning dose. Once determined, dose level, duration of dosing, frequency of dosing, and meal conditions will remain consistent within a cohort. For any MAD cohort in Part C with BID dosing, both morning and evening doses must be administered on Day 14.

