### **3.4. Duration of Dosing**

The duration of dosing for each part will be as follows:

Part A (SAD): 1 day

Part B (MAD): 15 days (including PTM dosing for all subjects on Day -1)

Part C (Adaptive SAD and/or MAD): 1 or 15 days (including PTM dosing for all multiple-dose subjects on Day -1)

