## 8.6. Safety Analysis

All safety data collected on or after the date that study drug was first administered up to the date of last dose of study drug plus 14 days will be summarized by treatment group (according to the study drug received) or treatment sequence using the Safety Analysis Set. As appropriate, placebo-treated subjects will be pooled across Parts A, B, and C of the study.

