## **8.10. Sample Size**

Due to its exploratory nature and no reliable variability estimation, no formal power or sample size calculations were used to determine the sample size for this study. Empirically, a sample size of 100-150 subjects (10 subjects per cohort, including 8 active and 2 placebo) was selected to provide an adequate characterization of safety, PK, and PD of TLC-2716.

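### Protocol and SAP give different placebo pooling rules and neither is defined by regimen, so single-dose and 14-day placebo subjects could share one comparator in Part C or under cross-part pooling

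*Combined protocol and SAP*

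**What the plan says.** There are three statements on placebo pooling for safety.

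- SAP 3.1: "Subjects dosed with placebo will be analyzed as 1 group in each part".
- Protocol 8.6: "As appropriate, placebo-treated subjects will be pooled across Parts A, B, and C of the study".
- Protocol synopsis, safety methods: "As appropriate, data from placebo-treated subjects will be pooled across Parts A, B, and/or C".

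Nothing says when cross-part pooling is appropriate, and no passage reconciles the protocol with the SAP. SAP 4.2 mentions pooled placebo subjects in all three parts without saying how they are grouped. SAP 3.1 specifies the by-cohort display only for Parts A and B, so the layout for Part C is left open.

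Each cohort has "10 subjects per cohort, including 8 active and 2 placebo". Protocol 3.4 fixes the regimen in the first two parts: "Part A (SAD): 1 day" for Part A, and 15 days for Part B including the placebo run-in day. Part C can hold either regimen, since its subjects are treated "for either 1 day (as in Part A) or 14 days (as in Part B" (protocol 3.1.3).

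**The concern.** With two placebo subjects per cohort, the pooled group is the working comparator for safety. Incidence of adverse events and of laboratory abnormalities are both primary endpoints (protocol 8.1.2). The SAP summarises the first as the percentage of subjects with at least one treatment-emergent event (7.1.6.3) and the second by each subject's worst grade after dosing (7.2.2.1). Neither measure is adjusted for time observed or number of samples, so both rise with longer observation and more draws.

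If single-dose and 14-day placebo subjects are put together, the pooled rate falls between the two regimens' rates. An inert drug would then look worse than placebo in a multiple-dose cohort and better than placebo in a single-dose cohort. Adding subjects to a mixed pool does not remove this. The second direction deserves as much attention as the first, because it flatters the single-dose arms.

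**Working it through.** **Counts.** The plan's own figure reproduces: 15 cohorts × 10 = 150 subjects (100 without Part C). At 2 placebo per cohort there are 10 in Part A, 10 in Part B and up to 10 in Part C, at most 30. The documents give no placebo event rate and plan no power calculation, so every rate below is an assumption.

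**Observation per regimen.**

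- Adverse events are collected until 14 days after the last dose (protocol 7.3.1.1): about 15 days for single-dose and 28 days for multiple-dose subjects.
- Post-dose laboratory draws (protocol 6.7.5.1, Tables 5 and 6): single-dose, Day 1 at 12 h, Days 2, 3, 4 and follow-up = 5; multiple-dose, Day 1 at 12 h, Days 2, 3, 5, 7, 10, 14, 17 and follow-up = 9.

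**Adverse events, inert drug, constant hazard.** Let pM be the multiple-dose placebo incidence. Then λ = −ln(1 − pM)/28 and the single-dose incidence is pS = 1 − exp(−15λ). Pooling Parts A and B gives (10·pS + 10·pM)/20.

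| Assumed pM | pS | Pooled A+B | Shift, each way |
|---|---|---|---|
| 20% | 11.3% | 15.6% | 4.4 points |
| 30% | 17.4% | 23.7% | 6.3 points |
| 50% | 31.0% | 40.5% | 9.5 points |
| 70% | 47.5% | 58.8% | 11.2 points |

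Pooling all three parts at pM = 30%, with five Part C cohorts, gives a shift of 4.2 to 8.4 points for either regimen, depending on the Part C mix.

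**Adverse events under the SAP rule.**

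- Part A: 10 placebo subjects, all single-dose; shift 0.
- Part B: 10 placebo subjects, all 14-day; shift 0.
- Part C with one regimen only: shift 0.
- Part C with 2 single-dose and 3 multiple-dose cohorts, pM = 30%: pooled (4 × 17.4 + 6 × 30.0)/10 = 25.0%. Multiple-dose looks 5.0 points worse and single-dose 7.6 points better.
- Over all mixed splits of five Part C cohorts at pM = 30%, the shifts run from 2.5 to 10.1 points. At pM = 70%, the most lopsided split (4 to 1) reaches 18.0 points for the regimen with one cohort.

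**Worst-grade laboratory abnormality, Parts A and B pooled.** With chance q per draw and independent draws, incidence is 1 − (1 − q)^5 for single-dose and 1 − (1 − q)^9 for multiple-dose.

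| Assumed q | Single-dose | Multiple-dose | Pooled | Shift, each way |
|---|---|---|---|---|
| 1% | 4.9% | 8.6% | 6.8% | 1.9 points |
| 3% | 14.1% | 24.0% | 19.1% | 4.9 points |
| 5% | 22.6% | 37.0% | 29.8% | 7.2 points |
| 10% | 41.0% | 61.3% | 51.1% | 10.2 points |

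**Against sampling error.** The Clopper-Pearson 95% interval for 3 of 10 is 6.7% to 65.2%, for 6 of 20 it is 11.9% to 54.3%, and for 9 of 30 it is 14.7% to 49.4%.

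**Pooling by regimen.** For an inert drug under the same assumptions the shift is 0 whatever the Part C mix, with 10 to 20 placebo subjects per regimen if Parts A and B complete.

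**The case against.** The sponsor has a good reply on scope. A reader might infer from SAP 3.1 that pooling by part puts single-dose and 14-day placebo subjects together throughout, so that the planned safety rates are skewed. The documents do not support that. In Cohorts 1-10 part and regimen coincide, so the SAP rule already pools by regimen there. Part C is optional and may run one regimen or not run at all. The protocol's cross-part pooling is discretionary, and the SAP, written later and based on protocol Amendment 1, can be read as using that discretion to choose the narrower pool.

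Many displays are also unaffected or largely so. Protocol 8.6.3 summarises graded laboratory abnormalities by cohort and treatment. Numeric laboratory values and vital signs are summarised by visit (SAP 7.2.1, 7.2.3), and ECGs by cohort and intervention at each time point (SAP 7.2.4). No formal laboratory testing is planned, and the countable study stopping criteria in protocol 3.3.2 count only subjects given active drug, so those counts do not use the placebo pool.

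The illustrations are also generous. Repeat results in one person are usually positively correlated, which would narrow the gap between 5 and 9 draws. Adverse events clustered soon after first dosing would narrow the other gap.

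All of this stands and limits the point. It does not settle which document governs, when cross-part pooling would be used, or how Part C placebo subjects are grouped if both regimens run.

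**Conclusion.** The point holds in a limited form. The protocol and SAP pooling rules conflict, and neither is defined by regimen. The mismatch would arise in Part C under the SAP if both regimens are run there, and under the protocol option whenever Parts A and B are combined. In those cases two primary safety summaries, crude treatment-emergent adverse event incidence and worst-grade laboratory incidence, would be shifted against the multiple-dose arms and in favour of the single-dose arms.

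The main illustrative cases give about 2 to 11 points. Only a lopsided regimen mix combined with a high assumed incidence gives more. The sizes rest on assumed rates, a constant adverse event hazard and independent laboratory draws, so the laboratory figures are upper-end. The shift is smaller than the imprecision of 10 placebo subjects and affects descriptive reading only. It still merits correction, because its direction is predictable and the remedy is cheap.

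**What to change.** Replace the placebo sentence in SAP 3.1 with wording such as:

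*Placebo subjects are pooled by regimen: single-dose (Part A and any single-dose Part C cohorts) and multiple-dose (Part B and any multiple-dose Part C cohorts). In the adverse event and worst-grade laboratory tables each active group is shown against the pool for its own regimen. Single- and multiple-dose placebo subjects are not combined.*

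Align protocol 8.6 and the synopsis with it. No change is shown to be needed for the by-visit vital-sign, ECG or numeric laboratory tables.

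The cost is wording and table shells, with no new data. Denominators are smaller than under pooling across all parts: 10 to 20 per regimen instead of up to 30. Compared with the SAP rule, the Part A and Part B pools stay the same or grow as Part C subjects join them. Once- and twice-daily, or fed and fasted, placebo subjects could still share a pool, but within a regimen they follow the same safety laboratory schedule and follow-up, so the artefact described here does not return.

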#### **3.2. Confidence Interval**

The Clopper-Pearson method will be used to calculate the confidence interval of the proportion, unless otherwise stated.

#### **3.3. Analysis Visit Windows**

Measurements will be allocated to an analysis visit date on case report forms (CRFs) collected based on the Schedule of Assessments in the protocol. The data reported at discontinuation will be treated as data at discharge.

##### **3.3.1. Data Handling Conventions and Transformations**

In general, age (in years) on the date of the first dose of study drug will be used for analyses and presentation in listings. If an enrolled subject was not dosed with any study drug, the randomization date will be used instead of the first dosing date of study drug. If only the birth year is collected on the CRF, “01 July” will be used for the unknown day of birth and month for the purpose of age calculation. If only birth year and month are collected, “01” will be used for the unknown day of birth.

Non-PK data that are continuous in nature but are less than the lower limit of quantitation (LOQ) or above the upper LOQ will be imputed as follows:

- A value that is 1 unit less than the lower LOQ will be used to calculate descriptive statistics if the datum is reported in the form of “< x” (where x is considered the lower LOQ). For example, if the values are reported as < 50 and < 5.0, values of 49 and 4.9, respectively, will be used to calculate summary statistics. An exception to this rule is any

value reported as  $< 1$  or  $< 0.1$ , etc. For values reported as  $< 1$  or  $< 0.1$ , a value of 0.9 or 0.09, respectively, will be used to calculate summary statistics.

- A value that is 1 unit above the upper LOQ will be used to calculate descriptive statistics if the datum is reported in the form of “ $> x$ ” (where  $x$  is considered the upper LOQ). Values with decimal points will follow the same logic as the bullet point above.
- The LOQ will be used to calculate descriptive statistics if the datum is reported in the form of “ $\leq x$ ” or “ $\geq x$ ” (where  $x$  is considered the lower or upper LOQ respectively).

If methods based on the assumption that the data are normally distributed are not adequate, analyses may be performed on transformed data or nonparametric analysis methods may be used, as appropriate.

Natural logarithmic transformation will be used for analyzing concentrations and PK parameters. Concentration values that are below the limit of quantitation (BLQ) will be presented as “BLQ” in the concentration data listing. Values that are BLQ will be treated as 0 at predose time points, and one-half the value of the LOQ at postdose time points for summary purposes.

The following conventions will be used for the presentation of summary and order statistics:

- If at least 1 subject has a concentration value of BLQ for the time point, the minimum value will be displayed as “BLQ.”
- If more than 25% of the subjects have a concentration data value of BLQ for a given time point, the minimum and Q1 values will be displayed as “BLQ.”
- If more than 50% of the subjects have a concentration data value of BLQ for a given time point, the minimum, Q1, and median values will be displayed as “BLQ.”
- If more than 75% of the subjects have a concentration data value of BLQ for a given time point, the minimum, Q1, median, and Q3 values will be displayed as “BLQ.”
- If all subjects have concentration data values of BLQ for a given time point, all order statistics (minimum, Q1, median, Q3, and maximum) and summary statistics will be displayed as “BLQ.”

PK parameters that are BLQ will be imputed as one-half LOQ before log transformation or statistical model fitting.

### **3.4. Visit Windows**

#### **3.4.1. Definition of Predose and Postdose**

The predose value associated with a treatment is defined as the last available value collected prior to the time of the first dose of the treatment (TLC-2716 or placebo) for the planned cohort

on Day -1, which may occur after placebo treatment of all subjects in MAD cohorts in Part B and C on Day -2.

Postdose value associated with a treatment is defined as any value collected after the first dose of that treatment and on or before the date of the last dose of that treatment plus 30 days, or before the time of the first dose of the following treatment, whichever comes earlier.

### **3.4.2. Analysis Visit Windows**

The nominal visit as recorded on the CRF will be used when data are summarized by visit. Any data relating to unscheduled visits will not be assigned to a particular visit or time point and in general will not be included in summaries. However, the following exceptions will be made:

- An unscheduled visit prior to the first dose of study drug may be included in the calculation of predose value, if applicable.
- For subjects who discontinue from the study, early termination (ET) data will be summarized as a separate visit, labeled as “Early Termination”.
- Data collected on a follow-up visit will be summarized as a separate visit and labeled “Follow-up”.

### **3.4.3. Selection of Data in the Event of Multiple Records on the Same Day**

If multiple valid, nonmissing numeric observations exist on a day, records will be chosen based on the following rules if a single value is needed:

- For predose, the last available record on or prior to the date and time of the first dose of study drug will be selected. If there are multiple records with the same time or no time recorded on the same day, average (arithmetic or geometric mean, as appropriate) will be used for the predose value. Of note, predose collections which occur in MAD cohorts on dosing days after Day 1 will not be included in the predose value averaging.
- For postdose values:
  - The record closest to the nominal day for that visit will be selected.
  - If there are 2 records that are equidistant from the nominal day, the later record will be selected.
  - If there is more than 1 record on the selected day, the average will be taken, unless otherwise specified.

If multiple, valid, nonmissing categorical observations exist on a day, records will be chosen based on the following rules if a single value is needed:

- For predose, the last available record on or prior to the date and time of the first dose of study drug will be selected. If there are multiple records with the same time or no time recorded on the same day, the value with the lowest severity will be selected (e.g., normal will be selected over abnormal for safety ECG findings).
- For postdose values, follow the same rules described above for postbaseline numeric observations, except that if there are multiple records on the same day, the most conservative value will be selected (e.g., abnormal will be selected over normal for safety ECG findings).

### **3.5. Missing Data**

Missing data can have an impact on interpretation of trial data. As this study is of short duration, it is anticipated that missing data will be minimal. In general, values for missing data will not be imputed. However, a missing pre-treatment laboratory result would be treated as normal (i.e., no toxicity grade) for the laboratory abnormality summary. All statistical analyses will be based on observed case unless otherwise stated.

